**Methods:**

We will conduct a cross-jurisdictional, multi-site implementation-effectiveness type II hybrid RCT. Eligibility criteria are: ≥65 years, diabetes diagnosis (Type 1 or 2) and at least one other chronic condition, and enrolled in a primary care or diabetes education program. Participants will be randomly assigned to the intervention (ACHRU-CPP) or control arm (1:1 ratio). The intervention arm consists of home/telephone visits, monthly group wellness sessions, multidisciplinary case conferences, and system navigation support. It will be delivered by registered nurses and registered dietitians/nutritionists from participating primary care or diabetes education programs and program coordinators from community-based organizations. The control arm consists of usual care provided by the primary care setting or diabetes education program. The primary outcome is the change from baseline to 6 months in mental functioning. Secondary outcomes will include, for example, the change from baseline to 6 months in physical functioning, diabetes self-management, depressive symptoms, and cost of use of healthcare services. Analysis of covariance (ANCOVA) models will be used to analyze all outcomes, with intention-to-treat analysis using multiple imputation to address missing data. Descriptive and qualitative data from older adults, caregivers and intervention teams will be used to examine intervention implementation, site-specific adaptations, and scalability potential.

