Laboratory values	HbA1c, e-GFR, LDL cholesterol	CT	T_1_, T_2_	Descriptive analyses, Inferential statistical analysis of T1-T2 change
Caregiver strain	Modified Caregiver Strain Index (CSI) – 13 items [74]	CG	T_1_, T_2_	Descriptive analyses T1-T2 (Treatment Effect); ANCOVA
Utilization of health and social services and associated costs	Health and Social Services Utilization Inventory (HSSUI) [75, 76]	CT, CG	T_1_, T_2_	Descriptive analyses T1-T2 (treatment Effect); Parametric or non-parametric tests depending on distributional properties of cost data, complete case analysis, Hazard Ratio (95% CI) & Risk Difference (95% CI) for ED visits and hospital admissions
Interprofessional team functioning	Partnership Self-Assessment Tool (PSAT) [77]	INT	3 months and end of intervention	Descriptive analyses
Public and community partner engagement	The Quality Involvement Measure [78] The Patient-Centred Outcomes Research Institute’s Ways of Engaging – Engagement Activity (WE-ENACT) Tool [79] Selected items of the Patient-Centred Outcomes Research Institute’s Engagement Activity Inventory (NET-ENACT) Tool [80]	Public and community research partners	3 months and end of intervention	Descriptive analyses

^a^ Four study groups: CT: client; CG: caregiver; INT: intervention team; Public and community research partners.

^b^ Two time points: T_1_: baseline; T_2_: 6 months after baseline.

^c^ PSAT will be completed by core intervention team (e.g., Registered Nurse, Registered Dietitian/Nutritionist, Program Coordinator)

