#### Analysis: effectiveness evaluation (older adult and caregiver participants)

The baseline demographic and clinical characteristics of participants who completed both the baseline and 6-month assessments will be compared. Descriptive statistical analysis will be used to summarize outcome variables at baseline and 6 months. For continuous variables, means and standard deviations will be calculated, and for categorical variables, frequencies and proportions will be assessed. Analysis of covariance (ANCOVA) will be used to test the differences in outcome variables between the intervention and control group at 6 months. Separate ANCOVA models will be run for each primary and secondary outcome, with the 6-month change in the outcome as the dependent variable, group (intervention, control) as the independent variable, and the baseline value of the outcome as the covariate.

Statistical tests will use a 0.05 two-tailed level of significance and 95% confidence levels. An intention-to-treat (ITT) approach unadjusted for baseline characteristics will represent the primary analysis, using multiple imputation for missing data. Costs will be applied to the health and social service use reported by clients and caregivers. Group differences in the 6-month change in service use costs will be examined using parametric or non-parametric methods, depending on the distributional properties of the cost data [83].

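### The cost analysis departs from the plan's own baseline-adjusted ANCOVA rule: it names tests on 6-month cost change with no baseline covariate, and the two statements need to be reconciled

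*Protocol article*

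**What the plan says.** The abstract of the protocol article states: "Analysis of covariance (ANCOVA) models will be used to analyze all outcomes". The section on analysis of effectiveness in older adults and caregivers gives the detail: "Separate ANCOVA models will be run for each primary and secondary outcome, with the 6-month change in the outcome as the dependent variable", group as the independent variable, "and the baseline value of the outcome as the covariate". The research questions list costs of health service use among the secondary outcomes, so this rule covers costs.

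Later in the same analysis section, costs get a sentence of their own: "Group differences in the 6-month change in service use costs will be examined using parametric or non-parametric methods", the choice depending on how the cost data are distributed. The Table 1 row for service use and costs reads "Parametric or non-parametric tests depending on distributional properties of cost data, complete case analysis", followed by hazard ratios and risk differences for emergency visits and admissions. The rows for the scored scales name ANCOVA; the cost row does not.

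Table 1 lists the service-use inventory (HSSUI) at T1 and T2 for clients and caregivers, and the data collection section says secondary outcome variables are measured at baseline. A baseline cost is therefore planned for each participant.

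**The concern.** The article gives two answers to how costs will be compared. If the cost-specific wording governs, the analysis is most naturally a t-test or rank test on change, with baseline cost entering only by subtraction. That fixes the slope of 6-month cost on baseline cost at 1, whatever the data show. When baseline cost predicts later cost weakly, subtraction adds noise and over-corrects chance imbalance. Skewed costs make such imbalance likely, because a few heavy users can land in one arm.

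The stake is the stated expectation that the intervention will be cost neutral because its cost is offset by lower acute care use. That is a claim about mean cost. A needlessly wide interval answers it poorly, and a non-significant result from a noisy test is easily misread as neutrality. Costs also feed the scalability assessment.

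**Working it through.** **Plan's own figure.** The plan gives no SD, correlation or target difference for costs. Its only calculation is for the MCS (264 = 2 × 110 × 1.2, which reproduces), and that has no bearing here.

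**Which rule governs costs.** Three features point to a separate, unadjusted analysis:
- The distribution-dependent wording appears twice, and Table 1 speaks of tests.
- The cost row specifies complete cases, whereas the main analysis uses multiple imputation.
- Table 1 overrides the general rule elsewhere: food security is listed as a secondary outcome, yet its row is descriptive only.

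Against this stands the general ANCOVA rule, which no sentence withdraws for costs.

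**Precision.** Let s1 and s2 be the SDs of cost at T1 and T2, and rho their correlation.
- Change score: variance s2² + s1² − 2·rho·s1·s2.
- Baseline-adjusted: residual variance (1 − rho²)·s2².
- Difference: (s1 − rho·s2)², which is never negative. Apart from estimating one slope, adjustment does not lose precision even when the two variances differ.

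With s1 = s2 these become 2(1 − rho) and 1 − rho² in units of s², and the ratio of change score to adjusted is 2/(1 + rho). Since rho is not in the document, a range is assumed:

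| rho | 2(1 − rho) | 1 − rho² | Variance ratio | Extra SE of change score |
|---|---|---|---|---|
| 0.3 | 1.40 | 0.91 | 1.54 | 24% |
| 0.5 | 1.00 | 0.75 | 1.33 | 15% |
| 0.7 | 0.60 | 0.51 | 1.18 | 8.5% |

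Below rho = 0.5, 2(1 − rho) exceeds 1, so the change score is noisier than ignoring baseline altogether. A low rho is plausible but not documented: costs include admissions, and the trial was halted in March 2020 while under way, so some participants' T1 and T2 may straddle that date.

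**Over-correction.** If the arms differ by D in mean baseline cost by chance, the change-score estimate has conditional expectation (effect) − (1 − rho)·D under equal variances. Per unit of D, the error is 0.7, 0.5 and 0.3 at the three correlations, in favour of the arm with the higher baseline cost. The adjusted estimate removes it.

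**Check with skewed data.** A simulation used lognormal costs, 106 per arm (about 264 less 20%, halved), 4,000 runs per setting, log-scale SD 1.0 or 1.5, log-scale correlation 0.3, 0.5 or 0.7, and no treatment effect.
- The adjusted estimate had 0.54 to 0.75 of the change-score variance. These ratios are lower than (1 + rho)/2 at the log-scale rho, partly because correlation is weaker on the cost scale. For SD 1.0 and log-scale 0.3 it is (e^0.3 − 1)/(e − 1) = 0.350/1.718 = 0.20, giving 1.20/2 = 0.60 against a simulated 0.594.
- The change-score estimate moved by −0.44 to −0.89 per unit of baseline imbalance; the adjusted estimate moved by −0.02 to 0.03.
- Both estimators averaged close to zero.

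**Rank route.** The formulas do not describe a rank test on change. Its defect is different: it does not estimate a difference in mean cost, which is the quantity that cost neutrality concerns.

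**The case against.** The strongest reply is that the ANCOVA rule already covers costs. That ANCOVA itself models 6-month change, so the word change does not signal an unadjusted test. A parametric method could be that very ANCOVA, with a non-parametric method as fallback, which is how the sensitivity analyses treat the primary outcome. This stands in part. A reader might infer that the plan definitely omits baseline cost, but the document does not say so. It contradicts itself, and the unadjusted analysis is the more natural reading of the cost wording.

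A second reply is that an article leaves model detail to an analysis plan and cites a source for the cost method. That would answer a complaint about missing detail. It does not answer two stated rules that disagree.

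Three stronger readings are tempting and are not supported:
- **That laboratory values have the same fault.** Their row reads "Descriptive analyses, Inferential statistical analysis of T1-T2 change". This leaves the method open and is compatible with the general ANCOVA, which also models change.
- **That the cost comparison is biased.** Under randomization the change score is unbiased on average; the issue is precision and conditional error given a chance imbalance.
- **That a loss of power can be quoted.** The only effect size in the plan, 0.38, belongs to the MCS. The cost hypothesis is neutrality, and no cost SD is given.

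**Conclusion.** The concern holds for costs, as an inconsistency whose more natural reading is an inferior analysis. On that reading, the change score's variance exceeds the baseline-adjusted one by a factor of about 1.54, 1.33 and 1.18 at rho of 0.3, 0.5 and 0.7. These factors rest on equal T1 and T2 variances and on assumed correlations. The equal-variance assumption is uncertain, since intervention-specific costs can arise only after baseline and in one arm; the direction of the comparison does not depend on it. The matter affects a secondary outcome in clients, and caregiver costs. The primary MCS analysis is already baseline-adjusted. It should be corrected, but it does not threaten the trial's main conclusion.

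**What to change.** In the analysis section and the Table 1 cost row, replace the choice between tests with one stated model: regression of 6-month cost on group and baseline (T1) HSSUI cost, reporting the adjusted difference in mean cost with a bootstrap or robust 95% CI. Ordinary regression of the 6-month value gives the same group difference as the plan's ANCOVA of change with baseline as covariate, so the cost analysis would then agree with the general rule. The interval method should accommodate skewness and zero costs. Zeros are likely among caregivers, whose use is described as emergency and hospital care, so a gamma model is unsuitable as it stands.

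The cost is a wording change in two places and slightly more analysis work. No new data are needed, and no further participants are lost, because a change score needs the T1 value too. As an optional clarification, the laboratory row could name the same ANCOVA.

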## Research aim, hypotheses and questions

The trial aims to evaluate the effectiveness and implementation of the ACHRU-CPP compared to usual care. We hypothesize that clients in the intervention compared to usual care group will experience greater improvements in mental and physical functioning and a range of other outcomes linked to health benefits (e.g., improved diabetes self-management, increased physical activity, reduced nutrition risk). We also expect that the intervention will be cost neutral relative to usual care because the intervention costs will be offset by lower use of other costly acute care services (e.g., hospitalization, ED use). Finally, we expect that the intervention will have potential for scale-up.

The study will address the following research questions regarding the six-month self-management intervention:What is the effect of the intervention compared to usual care on mental functioning (primary outcome) and physical functioning, diabetes self-management, depressive symptoms, anxiety, social support, physical activity, activities of daily living/instrumental activities of daily living, nutrition risk, food security, and costs of use of health services (secondary outcomes) in older adults aged ≥ 65 years with diabetes and one or more chronic conditions?What is the effect of the intervention compared to usual care on outcomes (health-related quality of life, depressive symptoms, anxiety, caregiver strain, costs of use of health services) of family and friend caregivers aged ≥18 years?Which subgroups of older adults (e.g., males/females, those with more/less chronic conditions) benefit most from the intervention?How is the intervention adapted and implemented in diverse settings?What is the scalability of the intervention?What are the experiences of older adults and caregivers who engage in the research process?

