#### Older adult participant outcomes and measures

The primary outcome is the mental function of the older adult participants as measured by the MCS score from the SF-12 [64]. This measure was chosen because functional status is a patient-reported outcome measure (PROM) recognized as important to a wide range of patients including those receiving self-management interventions targeting chronic conditions [81, 82]. We also found this measure to be responsive to the ACHRU-CPP in our previous trial [31] and mental functioning is linked to self-efficacy and the behaviour change constructs that play a central role in the theory underpinning the intervention. As shown in Table 1, a range of secondary outcome measures are also being assessed to capture physical functioning, activity levels, and limitations; diabetes self-management activities; various mental health outcomes; social support; nutrition risks; and clinical measures representing key diabetes risk factors such as measures of blood sugar control (HbA1c), kidney function (GFR), and cholesterol level (LDL) where available in electronic medical records.

The Health and Social Services Utilization Inventory (HSSUI) [46, 75, 76] will be used to measure the use of health and social services as reported by study participants. The six-month cost data will be derived from the product of the “quantity” data on the HSSUI and 2020-2021 “price” data obtained by our team from provincial databases. The costs of use of health and social services will include costs of intervention-specific services such as home/telephone visits and group wellness sessions.

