## Discussion

This paper describes the design of a multi-jurisdictional pragmatic implementation-effectiveness type II hybrid trial [47] of an intervention (ACHRU-CPP) aimed at improving self-management in older adults with diabetes and MCC. This study will make several important contributions to the existing knowledge base, including:A focus on a population of clinically-complex older adults (with diabetes and MCC), who are often excluded from RCTs.An evaluation of both effectiveness and implementation of the intervention, a hybrid design offering the potential to accelerate the translation of research findings into routine practice [47].Consideration of a large amount of quantitative as well as rich qualitative information about a broad range of outcomes. We have chosen objective, reliable, and valid measures to assess effectiveness and several quantitative and qualitative measures to assess implementation. The study also includes a cost analysis from a societal perspective which has been largely overlooked in previous studies of self-management interventions. Costing data will provide policy- and decision-makers with economic information needed to inform decision making related to integrating the intervention into usual care practice.Evaluation of the effectiveness and implementation of a self-management program before and during the COVID-19 pandemic. The intervention moved from in-person to virtual approaches with the onset of COVID-19. Information on the acceptability and experiences with in-person and virtual approaches to care from both client and provider perspectives will shed light on the strengths and limitations of each approach and may inform future clinical practice where we expect that elements of virtual delivery will remain in the post-pandemic period.A design with early consideration given to scale-up. We will collect data from many sources (e.g., clients, caregivers, providers, public and community research partners, decision-makers) related to the scalability of the intervention and strategies to facilitate successful scale-up.Insights regarding how to optimally engage patient and research partners in the development and implementation of a complex intervention. Active engagement of these groups is consistent with current recommendations for patient-oriented research [102, 103]. In our study, patients, caregivers, and members of the public at each site will be engaged in various ways such as serving as co-investigators, advising on the implementation of the intervention through membership on CABs and the Steering Committee, developing recommendations for sharing study results, and advising on scale-up planning. We will assess their experiences as research partners using various quantitative and qualitative measures.Complexity will be viewed as the intersection of the intervention and the context within which it is implemented, consistent with recent conceptualizations of complexity as it relates to the development and evaluation of healthcare interventions [49].

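### Cost neutrality is expected, but the planned cost analysis is a test of difference, which cannot support it and may not compare mean cost

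*Protocol article*

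**What the plan says.** Under Research aim, hypotheses and questions, the article states: "We also expect that the intervention will be cost neutral relative to usual care because the intervention costs will be offset by lower use". The lower use meant is that of acute care. The first research question in that section lists costs of health service use among the secondary outcomes.

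Under Analysis: effectiveness evaluation, the cost comparison is described as follows: "Group differences in the 6-month change in service use costs will be examined using parametric or non-parametric methods, depending on the distributional properties". The costs row of Table 1 calls these tests: "Parametric or non-parametric tests depending on distributional properties of cost data, complete case analysis". The general rule is: "Statistical tests will use a 0.05 two-tailed level of significance and 95% confidence levels".

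The cost variable includes the programme itself: "The costs of use of health and social services will include costs of intervention-specific services such as home/telephone visits and group wellness sessions". The Discussion gives the purpose: "Costing data will provide policy- and decision-makers with economic information needed to inform decision making". The scalability section places costs and benefits in Part A of the ISAT, which feeds the final recommendation on scale-up.

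The sample size section is built on mental functioning only. The article gives no margin, variance or power for costs, and no criterion for concluding neutrality.

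**The concern.** Neutrality is a statement that the cost difference is near zero. A two-sided test takes zero difference as its null hypothesis, so it can produce evidence against neutrality but none for it. A non-significant result may mean that costs are alike, or only that cost data are too variable for this sample size.

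The second problem is the quantity compared. Whether acute-care savings pay for the programme depends on mean cost, because means multiply up to total spending. Letting the distribution choose the test lets it also choose the quantity. If skewed costs lead to a rank test, the comparison is of ranks. Here that matters: each recipient of the programme carries some of its cost, while savings would fall on the few people who avoid an admission. Ranks can then differ although means are equal.

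At stake is the economic message to decision-makers and the costs and benefits rating in the scalability assessment.

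**Working it through.** **Completers per arm.** The article's own sample size reproduces: a standardised effect of 3.68/9.68 = 0.380, 80% power and two-sided 0.05 give 110 per arm by t-test, 220 in total, and 220 × 1.2 = 264. With the stated 20% attrition, 264 × 0.8 = 211.2 complete, or 105.6 per arm. There is no cost figure to reproduce.

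**Assumption.** The article gives no cost SD. I take the SD of the analysed cost variable as CV × mean cost, with CV from 1 to 2.

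**Precision, common SD.** SE = CV × √(2/105.6) = 0.1376 × CV, as a fraction of mean cost. The 95% half-width is 1.96 × SE:
- CV 1: 27% of mean cost
- CV 2: 54% of mean cost

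**Chance of a non-significant result when the programme is truly 30% dearer.** This is Φ(1.96 − 0.30/SE), the opposite tail being negligible or added in.
- Common SD, CV 1: 0.30/0.1376 = 2.18, giving 41%
- Common SD, CV 2: 0.30/0.2752 = 1.09, giving 81%
- SD proportional to the mean: SE = CV × √((1 + 1.3²)/105.6) = 0.1596 × CV. The ratios are 1.88 and 0.94, giving 53% (CV 1) and 84% (CV 2). The matching half-widths are 31% and 63%.

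**Could this sample support neutrality with a margin?** With a true difference of zero, the chance that the 95% interval lies wholly inside ±m (in SD units) is 2Φ(m/0.1376 − 1.96) − 1, or zero if that is negative:

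| Margin (SD units) | Chance |
|---|---|
| 0.25 | 0% |
| 0.30 | 17% |
| 0.38 | 58% |
| 0.50 | 91% |

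A margin of 0.30 SD is 30% of mean cost at CV 1 and 60% at CV 2. For 80% power at that margin, 2 × (1.96 + 1.2816)²/0.30² gives 234 completers per arm.

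**Rank test when true means are equal (simulation, assumed costs).** Control 6-month cost is lognormal with mean 4000 and CV 2. Intervention cost is lognormal with mean 3600 and CV 2, plus 400 for everyone. There are 105 per arm. The planned variable is change, so a lognormal baseline (mean 4000, CV 2) is subtracted. The Mann-Whitney test at 0.05 rejects in about 8% to 14% of trials at moderate to high baseline correlation. Across log-scale correlations of 0 to 0.7 it runs from about 7% to 15%, and the ends move by about a point between runs. The t-test rejects in 4% to 5%. A second assumed scenario adds a flat 300 to 900 per recipient, offset by fewer 10,000-unit admissions, with means again equal. There the rank test on change rejects in 10% to 44% of trials, against 4% to 5% for the t-test. The direction is the same, but the size depends heavily on the scenario.

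**The case against.** A reader might infer that the investigators intend to read a non-significant result as neutrality. The article does not say so. It also foresees 95% confidence levels, and an interval for the mean difference would show how large an increase remains possible. The misreading is a risk, not a plan. What stands is that no other basis for supporting the expectation is given.

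A reader might also infer that a rank test is planned. None is named. A bootstrap of the mean difference is a non-parametric method too, and the article summarises continuous variables by means and SDs in any case. The point about ranks is therefore conditional.

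The neutrality statement is worded as an expectation, and the matching research question asks about the effect on costs, which a between-group comparison does address. Costs were not used to size the trial. This makes the point less serious but leaves the mismatch.

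Finally, a margin is a detail that a condensed article may leave to a fuller document, so its absence alone would be no finding. The objection is to what the article does fix: a comparison of difference, with the method chosen by the distribution of the data, set against an expectation of no difference.

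**Conclusion.** The point holds in this form: the stated cost analysis cannot support the stated expectation, and one of its two branches may not address mean cost. Non-significance would be a common result even for a programme 30% dearer: about 41% to 81% of trials with a common SD, or 53% to 84% with the SD proportional to the mean. These figures rest on an assumed CV of 1 to 2 and about 105 completers per arm. They also ignore any gain from adjusting for baseline cost. The rank-test figures illustrate a mechanism under assumed costs and are not a prediction for this trial. Cost is a secondary outcome, so the primary conclusion on mental functioning is untouched. The change should be made because the cost result informs the advice on scale-up.

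**What to change.** In the effectiveness analysis section and the costs row of Table 1, replace the distribution-driven choice of test with one named quantity: the between-arm difference in arithmetic mean 6-month cost, including intervention costs, adjusted for baseline cost. Report it with a 95% confidence interval by a method suited to skewed costs, for example a bootstrap or a generalised linear model. Which of these is used is a matter of preference.

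State that neutrality will be claimed only if the interval lies within a margin that the investigators justify before unblinding. Otherwise the estimate and interval are reported as inconclusive on neutrality. If no margin can be justified, report the estimate and interval and make no neutrality claim.

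This costs some wording and one decision on a margin, with no new data. The price is candour: unless the margin is wide (near 0.5 SD on the assumptions above) or baseline adjustment helps considerably, the trial may well be unable to confirm neutrality even if it is true.
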